## Abstract

**Background:**

The development of probiotics as therapies to cure or prevent disease lags far behind that of other investigational medications. Rigorously designed phase I clinical trials are nearly non-existent in the field of probiotic research, which is a contributing factor to this disparity. As a consequence, how to appropriately dose probiotics to study their efficacy is unknown. Herein we propose a novel phase I ascending dose trial of *Bifidobacterium longum subsp. infantis* (*B. infantis*) to identify the dose required to produce predominant gut colonisation in healthy breastfed infants at 6 weeks of age.

**Methods/design:**

This is a parallel-group, placebo-controlled, randomised, double-blind ascending dose phase I clinical trial of dietary supplementation with *B. infantis* in healthy breastfed infants. The objective is to determine the pharmacologically effective dose (ED) of *B. infantis* required to produce predominant (>50 %) gut colonisation in breastfed infants at 6 weeks of age. Successively enrolled infant groups will be randomised to receive two doses of either *B. infantis* or placebo on days 7 and 14 of life. Stool samples will be used to characterise the gut microbiota at increasing doses of *B. infantis*.

**Discussion:**

Probiotic supplementation has shown promising results for the treatment of a variety of ailments, but evidence-based dosing regimes are currently lacking. The ultimate goal of this trial is to establish a recommended starting dose of *B. infantis* for further efficacy-testing phase II trials designed to evaluate *B. infantis* for the prevention of atopic dermatitis and food allergies in at-risk children.

**Trial registration:**

Clinicaltrials.gov #NCT02286999, date of trial registration 23 October 2014.

## Background

The idea of probiotics, “live microorganisms that when administered in adequate amounts confer a health benefit on the host”, dates back to Elie Metchnikoff who hypothesised over 100 years ago that lactic acid bacilli had health benefits [1]. To date, thousands of reports of probiotics have supported the potential health benefits of these bacteria and the World Health Organization (WHO) has formulated guidelines for their use as nutritional supplements as well as investigation into their potential therapeutic properties [2]. Probiotics have been studied for the treatment and prevention of a variety of diseases in children including atopic dermatitis, bacterial gastroenteritis, inflammatory bowel disease, and necrotizing enterocolitis [3–5]. Overall, the data concerning probiotics as preventive agents for atopic diseases such as atopic dermatitis and food allergies are inconclusive, with some studies suggesting a possible benefit and others showing mixed results [4, 6–8].

Humans and other mammals are hosts to a diverse set of symbiotic as well as pathogenic intestinal bacteria. Approximately 1000 microbial species reside at a density of 1 × 10^12^ organisms per gram of colonic content [9, 10]. Several studies have demonstrated a clear link between immune system development and the composition of gut microbiota [11–13]. In addition, disruption of intestinal barrier function may lead to premature exposure of the infant to atopy-inducing environmental allergens, which would theoretically predispose the infant to the development of food allergies [14]. By protecting against colonisation by pathogenic bacteria, probiotics may help protect intestinal barrier function and thus decrease the susceptibility for development of atopic diseases and food allergies [15]. However, the pharmacokinetics of commensal bacteria and the dosage required to achieve predominant gut colonisation has thus far not been quantified. The probiotic that will be administered in our proposed phase I clinical trial, *Bifidobacterium longum subsp. infantis (B. infantis),* is unique in that it is able to fully utilise human milk oligosaccharides [16]. Thus, an exclusively breastfed infant’s gut provides the ideal environment to facilitate colonisation with this commensal bacteria [16–18]*.*

In order to proceed with designing a rigorous phase II clinical trial program to evaluate *B. infantis* as a preventative measure for a variety of childhood ailments, including atopic disease, it is necessary to first determine the pharmacologically effective dose (ED) of *B. infantis*. To date, pharmacologically guided phase I studies have not been conducted in the field of probiotics. We are thus proposing a phase I dose-escalation trial to evaluate the safety and pharmacokinetics of *B. infantis* supplementation when administered to healthy breastfed infants. The primary endpoint of the proposed trial is identification of the ED of *B. infantis*, defined as the dose required to produce predominant (>50 %) gastrointestinal colonisation in breastfed infants by 6 weeks of age. The 50 % value was chosen based on the proportion of *B. infantis* colonisation observed in breastfed infants in less-developed countries that have a low incidence of atopic disease compared to infants in the United States, specifically that seen in Bangladeshi infants [19, 20].

If successful, this study will be the first of its kind to establish a standardised dosing regime for probiotic supplementation in infants and will serve as a platform from which to design phase II and III trials to investigate the ability of *B. infantis* to protect against the development of a variety of childhood illnesses, including atopic dermatitis and food allergies.

## Methods/Design

### Study design

The proposed phase I clinical trial is a parallel-group, placebo-controlled, randomised, double-blind ascending dose study of dietary supplementation with *B. infantis* in healthy breastfed infants to evaluate its safety as well as determine the ED of *B. infantis* producing >50 % gut colonisation at 6 weeks of age. Infants will be enrolled sequentially in groups of five (three randomised to receive *B. infantis* and two to receive placebo). The trial participants and investigators will be blinded as to their group randomisation, which will be conducted by the study pharmacist (who will then dispense blinded *B. infantis* or placebo to the investigators). Depending on group assignment, each infant will receive one dose of either *B. infantis* or placebo on day 7 and another on day 14 of life (two doses total). For infants in the *B. infantis* group, a calculated maximally recommended starting dose (MRSD) will be used to initiate the dose escalation and is defined below. Every 2 weeks, an additional group of five infants (randomised 3:2 to *B. infantis* and placebo) will be enrolled to receive progressively higher doses of *B. infantis*. Calculation of the appropriate dose escalation will be performed using a modified Fibonacci series as described below in an effort to identify the ED of *B. infantis*.

After the ED of *B. infantis* has been identified (defined as the dose capable of producing 50 % gut colonisation by 6 weeks of age) two additional sequential dose escalations will be performed. The purpose of the final two dose escalations is to determine if successively higher doses of *B. infantis* result in increased gut colonisation or barrier protection, or, alternatively, if a maximum effective dose (MaxED) for *B. infantis* exists above which there is no further increase in gut colonisation or barrier protection. Following the final dose escalation, Hanley’s Rule of Three will be applied in order to determine if lower-frequency adverse events are caused by *B. infantis*. Hanley’s Rule of Three states that in order to identify any adverse events occurring at a frequency of 1:10 or greater with a 95 % confidence interval, at least 30 subjects must be enrolled [21]. A schematic overview of the trial design and dose escalation protocol is provided in Fig. 1.

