**Fig. 1 Fig1:**
[figure not shown]
A parallel-group, placebo-controlled, randomised, double-blind ascending dose phase I study of dietary supplementation with *B. infantis.* Groups of healthy infants will receive increasing doses of *B. infantis* until it comprises 50 % of their gut microbiota, defined as the pharmacologically effective dose (*ED*). This figure arbitrarily designates Group 6 as receiving the ED of *B. infantis*. After the ED has been reached, two additional dose escalations will occur to determine the impact that additional *B. infantis* has on the gut microbiota. To satisfy Hanley’s Rule of Three, 30 infants will receive the highest dose of *B. infantis*. “*X*” represents the maximum recommended starting dose (*MRSD*). A modified Fibonacci Series (X, 2X, 3X, …) is used to guide the dose escalations. *CFU* colony-forming units

Study visits will be scheduled for weeks 1, 2, 6, 24, 36, 52, and 78. Parents will complete surveys at each study visit to monitor the infants for potential adverse events associated with probiotic administration including feeding intolerance, fevers, or bowel irregularities including constipation and diarrhoea.

Stool samples will be collected twice weekly for the first 6 weeks of life then once weekly at weeks 24, 36, 52, and 78. Stool samples will be analysed to determine the relative abundance of *B. infantis* over time, and the overall diversity of the gut microbiota with and without *B. infantis* supplementation. Stools will also be analysed for milk oligosaccharides to verify consumption of breast milk and to correlate the proportion of human milk oligosaccharides and free sugar monomers seen in the infant stool at various levels of *B. infantis* colonisation.

Breast milk will be collected at 7, 14, 42, 120, and 180 days after the birth of the infant to determine the type and proportion of milk oligosaccharides present at various time points. The purpose of this analysis is to allow correlation of the type and amount of milk glycans present in breast milk with that in the infant stool samples.

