### Study-wide number of subjects

We propose a maximum sample size of 90 infants. Five infants (three to receive *B. infantis* supplementation and two to receive placebo) will be enrolled for the initial dose of *B. infantis*. An additional five infants will be enrolled at each dose escalation. Once the pharmacologically effective dose (ED) of *B. infantis* has been reached, two additional dose escalations will be performed (for reasons as described above). We estimate that the ED of *B. infantis* will be identified within seven dose escalations (35 infants). Accounting for the final two dose escalations will bring the total to 45 infants. Following the final dose escalation, 45 additional infants (27 to receive *B. infantis* and 18 to receive placebo) will be enrolled to screen for lower-frequency adverse events using Hanley’s Rule of Three [21]. This will bring the maximum enrollment number to 90 infants. If the ED of *B. infantis* required to produce 50 % gut colonisation at 6 weeks is not reached, then enrollment will be halted after 90 infants have been enrolled. Additional stopping rules are listed in the “Study Endpoints” section.

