The most common adverse effects described with probiotic use include diarrhoea, vomiting, and increased flatulence. Probiotics are known to be extremely safe, as evidenced by prior use in premature infants as well as in both adults and children with HIV [40, 41]. In Finland, the use of probiotic supplements (namely *Lactobacillus rhamnosous GG*) has increased dramatically over the past 20 years without evidence of a corresponding increase in the rate of lactobacillus bactermia [42, 43]. Probiotic supplementation has also been shown to be well tolerated without adverse effects in a recent randomised, double-blind, placebo-controlled trial comparing a combination of lactobacilli (*Lactobacillus salivarius* and *Lactobacillus paracasei*) and bifidobacteria (*Bifidobacterium animalis subsp. lactis* and *Bifidobacterium bifidum*) in pregnant women and infants, with the goal of assessing the safety of probiotic supplementation [44]. In this trial, enrolled women were treated with a total of 1 × 10^9^ colony-forming units of this probiotic regime daily for the last month of pregnancy and the regime was then administered to their infants from birth through to 6 months of age. There was no significant difference in the incidence of adverse events in either the maternal or infant groups, and no adverse events were attributed directly to the probiotic supplementation. There have been rare reports demonstrating the possibility of probiotic-related infectious complications, such as sepsis, bacteraemia, and endocarditis [45–47]. However, it is estimated that the risk of developing bacteraemia from ingested *Lactobacillus* probiotics is less than one in one million [48]. Though extremely rare, sepsis due to bifidobacterium has been described [49–51]. The described cases of bifidobacterium bacteraemia include one adult that developed incidental sepsis following acupuncture, and two infants that received *Bifidobacterium breve* or *Bifidobacterium longum* as a probiotic supplement. Of note, one infant was premature with extremely low birthweight and the other was full term with comorbid omphalocele. To date there are no reported instances of bacteraemia resulting from *B. infantis*; however, all study participants will be warned of the extremely low risk of such complications.

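### The Rule of Three is given the task of deciding whether adverse events are caused by B. infantis, but it has no control term and can only detect events or bound their rate

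*Protocol article*

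**What the plan says.** All references are to the protocol article.

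- **Study design.** After the last dose escalation the Rule of Three "will be applied in order to determine if lower-frequency adverse events are caused by" the product. The next sentence describes the rule differently, as a means "in order to identify any adverse events occurring at a frequency of 1:10 or greater with a 95 % confidence interval", for which at least 30 subjects are needed.
- **Caption of Fig. 1.** "To satisfy Hanley’s Rule of Three, 30 infants will receive the highest dose of" B. infantis.
- **Study-wide number of subjects.** The extra cohort is 45 infants, 27 active and 18 placebo, "and 18 to receive placebo) will be enrolled to screen for lower-frequency adverse events using Hanley’s Rule of Three". The maximum enrolment is 90.
- **Safety, under Study endpoints.** Safety is an additional primary endpoint. The events named are fever, abdominal pain or colic, blood or purulence in the stool, diarrhoea and vomiting.
- **Tables 1 and 2.** Adverse event surveys run to week 78, with no difference by arm.

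The Rule of Three is the only analysis the article names for the extra cohort. No section states a comparison of adverse event rates between arms, and none rules one out.

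**The concern.** The stated purpose is causal attribution, but the method named for it concerns the rate in a single group. The rule has no term for what happens to infants who do not receive the product, so the 18 placebo infants in the extra cohort do not enter it.

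This matters for three reasons. Safety is a primary endpoint. The step takes 45 of the maximum 90 infants. And several of the named events, such as fever, vomiting and diarrhoea, can plausibly occur in untreated infants over 78 weeks. For such events a zero count, which the upper bound needs, may be unlikely, and a non-zero count has no causal meaning without the placebo arm.

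The label of lower-frequency events could also be read too widely. The threshold is 1:10, so the cohort is informative about fairly common events only.

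**Working it through.** **Inputs from the article.** Target frequency 1:10; confidence 95% (sidedness not stated; the Rule of Three is a one-sided bound); 3:2 allocation in groups of five; at most nine escalation groups (45 infants), then 27 active and 18 placebo.

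- Highest dose: active 3 + 27 = 30; placebo enrolled alongside 2 + 18 = 20.
- Maximum over the trial: active 9 × 3 + 27 = 54; placebo 9 × 2 + 18 = 36.

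**Assumed, because the article gives none.** Background rates of 2%, 5% and 10% in untreated infants. For power, placebo rates from 0% to 30%.

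**1. The plan's own figure.** Rule of Three: n = 3/p = 3/0.10 = 30. Exact: n = ln(0.05)/ln(0.90) = 28.4, so 29. The stated 30 reproduces.

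**2. What 30 infants deliver.**

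- Chance of at least one event at a true rate of 10%: 1 − 0.9^30 = 95.8%.
- One-sided exact 95% upper bound for 0/30: 1 − 0.05^(1/30) = 9.5% (the rule gives 3/30 = 10%).
- The same bound for 0/54: 1 − 0.05^(1/54) = 5.4%.

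These are two forms of one equation, (1 − p)^n = 0.05. It contains no placebo count.

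**3. Seeing an event when the product does nothing.** P(at least one event in 30) = 1 − (1 − p)^30:

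| Assumed background rate | P(at least one event) | P(no event) |
|---|---|---|
| 2% | 45% | 55% |
| 5% | 79% | 21% |
| 10% | 96% | 4% |

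At a 10% background rate, the chance of seeing an event equals the detection probability in step 2. The observation is then the same whether the 10% comes from the product or from background.

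**4. What a comparison with placebo could show.** Exact two-sided Fisher test at 0.05, active 10% v placebo 0%:

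- 30 v 20: with 0/20 on placebo, 6/30 gives p = 0.069 and 7/30 gives p = 0.033, so seven events are needed. P(X ≥ 7 | n = 30, p = 0.10) = 2.6%.
- 30 v 36 (maximum pooled placebo): with 0/36, 3/30 gives p = 0.089 and 4/30 gives p = 0.038, so four are needed. P(X ≥ 4 | n = 30, p = 0.10) = 35%.

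For a 10-point excess over placebo rates of 0% to 30%, power is about 3% to 9% for 30 v 20 and 14% to 29% for 54 v 36. For 30 v 36 it falls from 35% at a placebo rate of 0% to 22% at 5% and 16% at 10%. A significance test is therefore a weak tool here; an estimate with its interval is the honest output.

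**The case against.** The strongest reply is that this is one loose clause. The sentence after it gives the rule its valid meaning, the section on subject numbers speaks of screening, and the figure of 30 is right. All of that stands, and it limits the severity. It does not remove the mismatch, because the clause names a purpose and a method that do not fit each other.

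Two stronger readings are tempting, and the article supports neither.

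- *A reader might infer that the trial's safety conclusion is invalid.* The article draws no safety conclusion and states no attribution rule for this cohort. Only the stated purpose of the rule is wrong.
- *A reader might infer that the placebo comparison is unused.* The design is randomised, blinded and placebo-controlled, with the same surveys in both arms. A between-arm analysis may sit in the full protocol or the SAP, neither of which is shown. What can be said is that the named method does not use the placebo infants.

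Three further objections stand in part:

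- Lower-frequency is a comparative term. Three treated infants would show a 1:10 event with probability only 1 − 0.9^3 = 27%, so 1:10 is rarer than an escalation group can detect. The article also states the threshold openly. Spelling out the limit is still worthwhile.
- The totals of 54 and 36 hold only at maximum enrolment. If the effective dose falls at Group 6, as Fig. 1 illustrates, there are eight groups, giving 8 × 3 + 27 = 51 active and 8 × 2 + 18 = 34 placebo.
- A placebo comparison of this size cannot settle cause either. That is a reason for modest wording, not for leaving attribution with a rule that has no control.

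**Conclusion.** The point holds as a method matched to the wrong purpose. The Rule of Three supports a statement about detection, or an upper bound of about 10% (exact 9.5%, one-sided) when no event is seen in 30 infants. It supports no statement about cause. With no product effect, at least one event in 30 treated infants would be seen with probability 45%, 79% or 96% at background rates of 2%, 5% or 10%. Those rates are assumptions; the detection and bound figures follow from the article's own numbers.

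The sample size needs no change. Severity is minor to moderate: the valid purpose already appears elsewhere in the article, but the clause concerns a primary endpoint and half of the maximum enrolment (45 of 90).

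**What to change.** 1. In Study design, replace the causal clause with the detection meaning, so that it agrees with Study-wide number of subjects: 30 infants at the highest dose give about a 95% chance of seeing at least one event of true frequency 1:10 or more. Say that the cohort screens for events of about that frequency or higher, not for rarer ones.
2. For event types not seen, report the one-sided exact 95% upper bound: 9.5% for 30 infants at the highest dose. For all active infants, use the number actually enrolled (5.4% if that is the maximum of 54).
3. For event types that occur, base attribution on the risk difference between active infants (highest dose, and all active) and placebo infants, with an exact 95% CI. Present this as estimation and state the low power: for 10% v 0%, about 3% with 30 v 20 and 35% with 30 v the maximum of 36 pooled placebo infants.

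If the full protocol or SAP already contains item 3, a cross-reference is enough.

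**Cost.** Wording and reporting only, with no added infants, visits or samples. The downside is a more modest safety claim.

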**Fig. 1 Fig1:**
[figure not shown]
A parallel-group, placebo-controlled, randomised, double-blind ascending dose phase I study of dietary supplementation with *B. infantis.* Groups of healthy infants will receive increasing doses of *B. infantis* until it comprises 50 % of their gut microbiota, defined as the pharmacologically effective dose (*ED*). This figure arbitrarily designates Group 6 as receiving the ED of *B. infantis*. After the ED has been reached, two additional dose escalations will occur to determine the impact that additional *B. infantis* has on the gut microbiota. To satisfy Hanley’s Rule of Three, 30 infants will receive the highest dose of *B. infantis*. “*X*” represents the maximum recommended starting dose (*MRSD*). A modified Fibonacci Series (X, 2X, 3X, …) is used to guide the dose escalations. *CFU* colony-forming units

Study visits will be scheduled for weeks 1, 2, 6, 24, 36, 52, and 78. Parents will complete surveys at each study visit to monitor the infants for potential adverse events associated with probiotic administration including feeding intolerance, fevers, or bowel irregularities including constipation and diarrhoea.

Stool samples will be collected twice weekly for the first 6 weeks of life then once weekly at weeks 24, 36, 52, and 78. Stool samples will be analysed to determine the relative abundance of *B. infantis* over time, and the overall diversity of the gut microbiota with and without *B. infantis* supplementation. Stools will also be analysed for milk oligosaccharides to verify consumption of breast milk and to correlate the proportion of human milk oligosaccharides and free sugar monomers seen in the infant stool at various levels of *B. infantis* colonisation.

Breast milk will be collected at 7, 14, 42, 120, and 180 days after the birth of the infant to determine the type and proportion of milk oligosaccharides present at various time points. The purpose of this analysis is to allow correlation of the type and amount of milk glycans present in breast milk with that in the infant stool samples.

Entry into the study requires the intent to breastfeed exclusively for a minimum of 6 months. If mothers decide to discontinue breastfeeding during the study, we will note that in the infant’s notes and obtain an additional series of weekly stool samples for 6 weeks after discontinuation of breastfeeding. The purpose of this additional stool sample collection is to determine if discontinuation of breastfeeding has an impact on the level of existing *B. infantis* colonisation in the infant gut.

A table of the schedule of study visits and specimen collections is provided in Table 1, and an overview of the timeline of the study interventions and assessments is provided in Table 2.

**Table 1 Tab1:** Schedule of study visits and specimen collections for each infant and mother

Week	Visits and activities
Prior to starting the study	• The patients’ parents or legal guardians will be asked to read and sign the consent form and will be instructed on the procedures for collection and storage of stool samples. They will be asked to refrain from giving the child any other dietary supplementation or probiotics while in the study and to inform the researchers if they are prescribed oral antibiotics at any time during the study.
Week 1	• Initial study visit, adverse event survey administration to parents and administration of first dose of *B. infantis* or placebo on day 7 of life.
	• Week 1 stool samples collected (infants will have stool samples collected twice weekly for the first 6 weeks and then at the study visits at weeks 6, 24, 36, 52, and 78).
	• If breastfeeding is discontinued at any point in the study, an additional series of six weekly stool samples will be collected following discontinuation in addition to the regularly scheduled collections
	• Mother collects breast milk on day 7 of life.
Week 2	• Study visit, adverse event survey administration to parents and administration of second dose of *B. infantis* or placebo on day 14 of life.
	• Week 2 stool samples collected
	• Mother collects breast milk on day 14 of life.
Week 3	• Week 3 stool samples collected
	• Adverse event survey administration to parents
Week 4	• Week 4 stool samples collected
	• Adverse event survey administration to parents
Week 5	• Week 5 stool samples collected
Week 6	• Study visit, adverse event survey administration to parents.
	• Week 6 stool sample collected.
	• Mother collects breast milk on day 42 of life.
Week 17	• Mother collects breast milk on day 120 of life.
Week 24	• Study visit, adverse event survey administration to parents.
	• Week 24 stool sample collected.
Week 25	• Mother collects breast milk on day 180 of life.
Week 36	• Study visit, adverse event survey administration to parents.
	• Week 36 stool sample collected.
Week 52	• Study visit, adverse event survey administration to parents.
	• Week 52 stool sample collected.
Week 78	• Study visit, adverse event survey administration to parents.
	• Week 78 stool sample collected.

**Table 2 Tab2:** Schedules for study participant enrolment, interventions and assessments in parallel-group, placebo-controlled, randomised, double-blind ascending dose phase I study of dietary supplementation with *B. infantis*

	Enrolment	Allocation	Post-allocation											
Timepoint	–t_1_	0	Week 1	Week 2	Week 3	Week 4	Week 5	Week 6	Week 17	Week 24	Week 25	Week 36	Week 52	Week 78
Enrolment:														
Eligibility screen	X													
Informed consent	X													
Allocation		X												
Interventions:														
Dose #1 of *B. infantis*/placebo			X											
Dose #2 of *B. infantis*/placebo				X										
Infant stool collection			X	X	X	X	X	X		X		X	X	X
Breast milk collection			X (Day 7 of life)	X (Day 14 of life)				X (Day 42 of life)	X (Day 120 of life)		X (Day 180 of life)			
Assessments:														
Identification of pharmacologically effective dose (ED) of *B. infantis*								X						
Study visit			X	X				X		X		X	X	X
Adverse event survey			X	X				X		X		X	X	X
Analysis of stool oligosaccharides			X	X	X	X	X	X		X		X	X	X
Analysis of stool microbiota			X	X	X	X	X	X		X		X	X	X
Analysis of breast milk oligosaccharides			X (Day 7 of life)	X (Day 14 of life)				X (Day 42 of life)	X (Day 120 of life)		X (Day 180 of life)			

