## Study methods and interventions

### Infant stool collection

Parents will be instructed how to collect and store infant stool samples at home. Stool samples will be collected twice weekly for the first 6 weeks of life then once weekly at weeks 24, 36, 52, and 78. If breastfeeding is discontinued at any point, an additional series of weekly stool samples will be collected for 6 weeks following discontinuation. At the initial enrollment visit parents will be provided with a stool sample collection including a sealable freezer box, marked sealed collection tubes and sealable plastic bags. Parents will be instructed to store samples in their home freezers immediately after collection to prevent secondary bacterial growth, and discard any samples not able to be frozen at the time of collection. Stool samples will be stored in the home freezers of study participants and picked up by study personnel once weekly to ensure they can be properly transported to the laboratory under temperature-controlled conditions. Any samples that are not stored immediately in the freezer at the time of collection or thaw en route to the laboratory will be discarded and parents will be instructed to collect and store a new stool sample according to the protocol. The stool samples will be analysed in the laboratory using DNA extraction to determine the identity and predominance of various commensal bacterial species, including the percentage of *B. infantis* present. The method of stool collection that will be provided to parents is described below:At any time of day, scoop 1–2 teaspoons of your infant’s stool with the tongue depressor into the sealable collection tube. The amount of stool should fill the tube between the 5 and 10 ml mark.Seal the tube and label with the time and date it was collected.Place the stool filled tube inside a sealable plastic bag and seal it.IMMEDIATELY place the sealed bag containing the stool sample into the study freezer box and store it in your freezer. It is important that stool samples are stored in the freezer immediately after collection to prevent bacteria from growing. If the stool sample was not immediately placed in the freezer, please discard the sample and collect another sample from your baby at the earliest convenience.

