#### Microbiota composition

In addition to determining the percent composition of *B. infantis* in infant stool samples, numerous other measures such as microbiota diversity (Shannon Diversity plots) and rate of *B. infantis* decline following cessation of breast feeding will also be determined.

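### No stool is tied to the time at or just before weaning, so the effect of stopping breastfeeding on B. infantis colonisation rests on a baseline that is often weeks to months old

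*Protocol article*

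**What the plan says.** The protocol article gives two aims for the period after weaning. Study design says the extra stools are to "determine if discontinuation of breastfeeding has an impact on the level of existing" B. infantis colonisation. Under Secondary outcome measures, Microbiota composition says that the rate of B. infantis "decline following cessation of breast feeding will also be determined".

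The sampling meant to serve these aims appears in three places, each time after the event:

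- Study design: "obtain an additional series of weekly stool samples for 6 weeks after discontinuation of breastfeeding"
- Table 1: "an additional series of six weekly stool samples will be collected following discontinuation in addition to the regularly scheduled collections"
- Infant stool collection: "an additional series of weekly stool samples will be collected for 6 weeks following discontinuation"

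The routine schedule (Infant stool collection) is: "Stool samples will be collected twice weekly for the first 6 weeks of life then once weekly at weeks 24, 36, 52, and 78".

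On the expected timing of weaning, Study design states: "Entry into the study requires the intent to breastfeed exclusively for a minimum of 6 months".

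**The concern.** Whether stopping changes an existing level is a before/after question, so it needs a measurement close to the time of stopping. The plan triggers none. The intended 6 months of exclusive breastfeeding puts weaning that goes to plan in the part of the schedule where routine stools are months apart.

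Suppose the first post-weaning stool is low. The fall may have come between the last routine stool and weaning, during a gradual changeover to other food, or after the last breastfeed. The data as scheduled often could not separate these. The Discussion presents the effect of stopping as part of what is distinctive about the trial, so the aim is not incidental.

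**Working it through.** The article gives no sample size or precision for this objective, so there is no stated figure to reproduce. The check is arithmetic on the schedule.

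**1. Gaps between routine stools** (weeks 6, 24, 36, 52 and 78, from Infant stool collection and Table 1). If weaning is equally likely at any time within a gap, the mean age of the last stool is half the gap.

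| Weaning in weeks | Gap = maximum age (weeks) | Mean age (weeks) |
|---|---|---|
| 6–24 | 24 − 6 = 18 | 9 |
| 24–36 | 36 − 24 = 12 | 6 |
| 36–52 | 52 − 36 = 16 | 8 |
| 52–78 | 78 − 52 = 26 | 13 |

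**2. Average for infants who reach the intended 6 months.** Assumptions: 6 months is about week 26, and weaning is uniform over weeks 26 to 78 (52 weeks).

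- Weaning in weeks 26–36 (10 weeks): the week-24 stool is 2 to 12 weeks old, mean 7.
- Weaning in weeks 36–52 (16 weeks): mean 8.
- Weaning in weeks 52–78 (26 weeks): mean 13.
- Overall mean = (10×7 + 16×8 + 26×13)/52 = 536/52 = 10.3 weeks.
- Over 4 weeks old: (8 + 12 + 22)/52 = 81%.
- Over 12 weeks old: (0 + 4 + 14)/52 = 35%.
- 2 weeks old or less: (0 + 2 + 2)/52 = 8%.

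**3. What the six post-weaning stools can estimate.** Assume they fall at weeks 1 to 6 after stopping, and that log abundance falls in a straight line with constant residual variance. The standard error of the slope is proportional to 1/√Sxx, where Sxx = Σ(week − mean week)².

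- Weeks 1–6, mean 3.5: Sxx = 2×(0.25 + 2.25 + 6.25) = 17.5.
- Weeks 0–6, mean 3: Sxx = 2×(1 + 4 + 9) = 28.0.
- Ratio of standard errors = √(28.0/17.5) = 1.26.

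The slope is estimable either way. Without a week-0 stool its standard error is about 1.26 times as large.

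**4. What is gone before the first stool.** With half-life h in weeks, the share of the level at weaning that remains at week 1 is 2^(−1/h). The documents give no half-life, so a range is shown.

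| Assumed half-life (weeks) | Remaining at week 1 |
|---|---|
| 0.5 | 25% |
| 1 | 50% |
| 2 | 71% |
| 4 | 84% |
| 8 | 92% |

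The unseen early fall matters if loss is fast and is modest if it is slow. In an infant that had lost B. infantis before the series began, the slope would be flat near zero and could be read as no decline.

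**The case against.** The strongest reply is that a reader might infer from the schedule that neither the impact of stopping nor the rate of decline can be measured. The documents do not support that, and these points stand:

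- **Rate of decline.** Microbiota composition asks for the rate after cessation, and six weekly stools after cessation can estimate it.
- **Never-colonised infants.** They are not confused with infants that lost B. infantis at weaning. Twice-weekly stools to week 6 show early colonisation, and each later routine stool shows whether it has lasted. Only loss between the last routine stool and weaning is ambiguous.
- **The 26-week figure.** It applies only to weaning just before week 78. Weaning at about week 26 follows the week-24 stool by roughly 2 weeks, and weaning in the first 6 weeks has a stool from the same week.
- **The trigger.** It is tempting to read it as the complete end of breastfeeding. The article does not define it, and the end of exclusive breastfeeding is a possible reading. An operational definition may well sit in the full protocol.
- **Weight.** This is a secondary matter. The effective dose at 6 weeks and safety are untouched.

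Two further mitigations help less. The oligosaccharide assay gives objective information on feeding, but only on stools that are collected, so it cannot fill a gap in collection. Infants still breastfed offer an age comparison, but it is non-randomised and available only at the four routine weeks.

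None of this supplies a sample near the time of stopping.

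**Conclusion.** The concern holds for the before/after aim and in part for the slope. As scheduled, the impact of stopping is measured poorly; it is not unmeasurable. For most infants who wean after the intended 6 months, the baseline would be more than 4 weeks old (81%, mean 10.3 weeks, worst case 26), and change due to weaning is confounded with change due to age and diet. The slope after cessation remains estimable, with less precision and without an observed starting level.

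The timing figures rest on uniform weaning over weeks 26 to 78. The precision figure rests on log-linear decline and stools at weeks 1 to 6. The gaps themselves come straight from the schedule. The change is worth making: it serves a stated secondary objective at low cost, and Trial status says recruitment had not begun.

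**What to change.** Amend Study design, Infant stool collection and Table 1 as follows:

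1. Ask mothers to tell staff when they plan to stop breastfeeding.
2. Collect one home stool at or before the last breastfeed, as the week-0 sample of the existing weekly series.
3. Record the dates of first formula, first solids and last breastfeed.
4. Measure change from the week-0 sample, in infants with B. infantis present in it.

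The cost is one extra home stool per weaned infant, with collection procedures already in place, and three dates. The week-0 stool brings the age of the baseline to about zero and raises Sxx from 17.5 to 28.0. The limitation is that abrupt, unannounced weaning will still leave some infants without the baseline; their number should be reported.
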